**Patients and Inclusion criteria:**

Premature infants with a birth weight ≤1500 g and a gestational age (GA) ≤32 weeks are eligible for inclusion in the study.

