**Statistics:**

**Sample size:**

Based on studies investigating meconium passage in VLBW infants [7], a sample size estimation [11] indicated that a total of 40 infants would suffice to detect a 20% difference in the outcome between the groups with a power of 80% and a significance level of 0.05

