**Primary outcome:**

time to complete Meconium evacuation in days.

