**Secondary outcome:**

introduction of enteral feeding in days, feeding volume on day 14th

time to full enteral feeding in days,

**Statistical analysis** :

Given the non-normal distribution of the data, all comparisons will be performed using non-parametric tests. The Mann-Whitney U test will be used to detect treatment effects between the groups. Kaplan-Meier curves will be plotted to visualize differences in the time to complete meconium evacuation between the groups. Comparison of the curves will be performed using the log rank test. Multiple Cox regression models will be used to identify the possible influence of the covariates birth weight and GA. For all tests, a p-value < 0.05 was considered to indicate statistical significance. SPSS statistical software system (SPSS Inc., Chicago, IL, version 10.0) will be used for all calculations.

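### The treatment comparison uses neither gestational age nor birth weight, although both are known at baseline and named as covariates; the cost is precision, not validity

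*Protocol*

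**What the plan says.** The primary outcome is "time to complete Meconium evacuation in days". The Statistical analysis paragraph, printed under the Secondary outcome heading, gives each method a purpose:

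- A general rule: "all comparisons will be performed using non-parametric tests".
- The treatment effect: "The Mann-Whitney U test will be used to detect treatment effects between the groups".
- The Kaplan-Meier curves: "Comparison of the curves will be performed using the log rank test".
- The covariates: "Multiple Cox regression models will be used to identify the possible influence of the covariates birth weight and GA".

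No stratum or covariate is attached to the Mann-Whitney or the log-rank test. Both covariates are available for every infant, because they define eligibility: "Premature infants with a birth weight ≤1500 g and a gestational age (GA) ≤32 weeks are eligible for inclusion in the study". The Data collection list also places them among the pre-treatment items. Under Design, randomisation is stratified by GA (below 28 weeks against 28 weeks or more) in blocks of 4. Birth weight is not a stratification factor.

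**The concern.** The plan names two covariates that might drive the outcome, collects both, and stratifies on one. It then tests the treatment without either. With about 20 infants per arm, whatever variation GA and birth weight explain stays in the noise against which osteopathy is judged. The one sentence that uses the covariates is worded as a question about the covariates, whereas the Aim and Hypothesis sections ask about the treatment. At stake is some of the 80% power that the Sample size section claims, and a treatment comparison that does not account for the factor used in the randomisation.

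**Working it through.** **Inputs.** From the Sample size section: "a total of 40 infants would suffice to detect a 20% difference in the outcome between the groups". The same section sets 80% power and a 0.05 level. Assumed because not stated: 1:1 allocation (20 per arm) and a two-sided test. The documents give no standard deviation and no correlation of birth weight or GA with the outcome, so every gain below is conditional on assumed values.

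**The plan's own figure.** The 40 cannot be reproduced, because the 20% has no scale and no spread is given. What 40 infants can detect at 80% power is a standardised difference of (1.960 + 0.842) × √(2/20) = 0.886. Read as a relative difference in mean days, that requires a coefficient of variation of 0.20/0.886 = 0.226. The steps below therefore start from 80% unadjusted power, not from the 20%.

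**Analytic gain.** If the covariates explain a share R² of the outcome variance, the residual SD is multiplied by √(1 − R²). Power becomes Φ(2.802/√(1 − R²) − 1.960), and the total needed for 80% power is about 40 × (1 − R²).

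| R² | Power with 40 | Total for 80% | CI width ratio |
|---|---|---|---|
| 0.10 | 84% | 36 | 0.95 |
| 0.20 | 88% | 32 | 0.89 |
| 0.30 | 92% | 28 | 0.84 |

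**Simulation with both covariates.** Settings: 40 infants, two GA strata, blocks of 4, a true effect of 0.909 SD (80% power by t test), birth weight-GA correlation 0.5-0.7, and R² for the two together of 0.12-0.31.

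- Mann-Whitney, unadjusted: about 76-80%.
- Rank analysis of covariance (ANCOVA) adjusting for both: about 82-89%.

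**Which covariate gives the gain.**

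- In six settings of 1,000 trials each, rank ANCOVA with the GA stratum alone, then with birth weight added, gave 83.4 to 84.3, 83.2 to 87.9, 78.8 to 85.0, 81.1 to 82.6, 84.0 to 88.7 and 80.3 to 88.8.
- With power near 85%, each figure has a standard error of √(0.85 × 0.15/1000) = 1.1 points, so the increment is best read as roughly 0-8 points.
- When GA enters as a continuous variable, adding birth weight changes power by about -1 to +2 points. It adds 2-7 only where birth weight is assumed to be the stronger predictor.
- The algebra agrees. With correlation r between the covariates and correlations b (birth weight) and g (GA) with the outcome, joint R² = (b² + g² − 2bgr)/(1 − r²). For b = g = 0.4 and r = 0.7 this is 0.096/0.51 = 0.188, against 0.16 for GA alone. Birth weight then explains (0.188 − 0.16)/0.84 = 3.4% of what GA leaves.

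**If birth weight is not prognostic.** Adding it to the stratum model took power from 78.0 to 76.7 and from 77.9 to 76.4, a loss of 1.3 and 1.5 points.

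**Type I error at 40 infants.** Rank ANCOVA rejected in about 4-6% of null trials. Covariate-adjusted Cox tests rejected in about 5-9% (likelihood ratio) and, in a separate simulation with a single covariate, 6-11% (Wald).

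**The case against.** The strongest case against has four parts.

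1. *The Cox sentence may already include arm.* It follows the between-group survival comparison and calls the variables covariates, so a model with arm, birth weight and GA is a natural reading. This stands. A reader might infer that the Cox models leave osteopathy out; the text neither says so nor rules it out. What the text does not do is state that an adjusted treatment effect will be reported, or that it carries the comparison.

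2. *Nothing is invalid.* This also stands. A reader might infer that a chance imbalance in birth weight biases the result. Under randomisation such imbalance is already part of the null distribution of the unadjusted tests, so the consequence is a less precise comparison. Stratifying on GA also partly balances birth weight to the extent that the two are correlated.

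3. *Birth weight is the weaker lever.* Largely right. A reader might take birth weight as the main loss, because it is the covariate that randomisation does not handle. But the GA strata are ignored in the treatment tests too. When GA is used as measured, birth weight adds little unless it dominates GA, and the documents give no support for assuming that. The point must cover both variables.

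4. *This can be left to a statistical analysis plan.* That would hold if the protocol were silent. It is not: it names the test for treatment effects and gives the covariates a different purpose.

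**Conclusion.** The point holds as a loss of efficiency. As written, the treatment comparison ignores GA and birth weight, and the Cox sentence leaves the role of arm open.

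Under an assumed joint R² of 0.12-0.31, adjusting for both is worth moving from about 76-80% to about 82-89% power, much of it from GA. The documents cannot confirm that range, and the gain disappears if neither variable is prognostic. It is not a finding of bias or of an inflated error rate in the planned tests. The change is worth making because the variables are already collected and the cost of being wrong is small.

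**What to change.** Amend the Statistical analysis paragraph in two places.

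1. **Primary comparison.** Pre-specify a rank-based analysis of time to complete evacuation on arm, GA (stratum or continuous, chosen in advance) and birth weight in grams. Rank ANCOVA serves if every infant has an observed time. If infants are censored, for example by transfer or discharge, regress log-rank scores on the same terms. This keeps to the plan's preference for non-parametric comparisons. The Mann-Whitney and log-rank tests can remain as unadjusted supporting analyses.

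2. **Cox model.** State that it includes arm, and that it reports the arm hazard ratio with 95% CI adjusted for birth weight and GA. Label it a supporting estimate, not the source of the primary p-value, because adjusted Cox tests can exceed 5% under the null with 40 infants. In a Cox model the benefit shows as power and a less attenuated hazard ratio, not as a smaller standard error of the log hazard ratio.

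The cost is a few sentences, no new data, and about 1 point of power if birth weight turns out not to be prognostic.

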**Duration of the study:**

Approximately 160-180 infants are administered to the neonatal intensive care unit/year. To recruit 40 patients it will take 4-6 months.

